### Transabdominal preperitoneal patch plastic repair (TAPP)

The abdomen will be accessed and the pneumoperitoneum will be achieved with standard laparoscopic techniques. The preperitoneal space will be exposed transabdominally with a sharp incision, followed by bluntly stripping the peritoneum that overlies the inguinal anatomy. An Ultrapro® mesh (Ethicon Inc., Johnson & Johnson, Somerville, NJ, USA) will be deployed and fixed in place with either staples or glue, and then the peritoneum will be returned to its anatomical position.

### Surgical technique

At an umbilical site, a Veress needle is inserted to induce a pneumoperitoneum, and then the needle is replaced with a 10 to 12 mm optical trocar. Next, two 5 mm trocars are positioned bilaterally on the umbilical line in the iliac fossa. An incision is made in the peritoneal wall, starting at the level of the superior margin of the internal inguinal ring and at the level of the epigastric vessels. The incision is extended medially, up to the residue of the umbilical artery, and then laterally, 3 to 4 cm past the inguinal ring; the total incision length is 7 to 8 cm. In the presence of a direct hernia, the hernial sac is directly isolated and reduced. In the case of an indirect or femoral hernia, the preperitoneal parapubic adipose tissue is carefully dissected medially to expose the horizontal pubic ramus and Cooper’s ligament. Accurate dissection of the preperitoneal retrovesical tissue facilitates positioning the mesh. The internal inguinal ring is explored, and the hernial sac is isolated and reduced; this maneuver is performed to reveal the presence of perihernial lipomas, which can then be removed. Once the spermatic cord is freed from the peritoneal wall, a macroporous, partially absorbable Ultrapro mesh (Ethicon) is positioned. This type of mesh allows the surgeon to view the underlying structures, which facilitates positioning the mesh. The mesh is cut to 10 × 13 cm and placed in the preperitoneal space such that it is in medial contact with the paravesical area, it covers Cooper’s ligament, it rests on the inguinal region, and it extends laterally over the epigastric vessels.

### Stapling

For this procedure, the mesh is fixed with an Endopath Multifeed Stapler with a 10 mm shaft and helical titanium staples (Protack, Covidien, Mansfield, MA, USA). The technique that we adopted involves positioning two metal clips at the level of Cooper’s ligament and the pubic tubercle. Additionally 4 staples are placed laterally at the level of the deep inguinal ring medially and laterally to the inferior epigastric vessels with absorbable staples (Securestrap, Ethicon). The peritoneal flap is then closed with four additional absorbable staples.

### Tisseel™ tissue glue

For this procedure, the mesh is anchored with 2 mL of fibrin glue (Tisseel, Baxter, Deerfield, IL, USA). Tisseel is applied to both anterior and posterior sides of the mesh with a dedicated laparoscopic tool (Duplotip, Baxter) inserted into a 5 mm trocar. To obtain optimal bonding between the Tisseel on the mesh and the peritoneal wall, slight pressure is applied to the mesh with the Duplotip. The Tisseel is applied to the entire perimeter of the mesh, and in particular, at the level of the superior margin, the “triangle of disaster,” in proximity of the prevesical fat, to assure good adhesion. The peritoneal flap is then closed with small, continuous, absorbable 2/0 sutures.

### Postoperative care

To reduce bias, the postoperative regime is standardized for the study. All patients will receive the same intra- and perioperative care, except for the mesh fixation technique. The postoperative care will also be uniformly administered, and changes will only be made when the patient’s comfort or safety is compromised. All patients will be mobilized as soon as possible during the postoperative period. All patients will receive paracetamol (three 1 g doses per 24 h), administered either intravenously (early postoperative course) or orally (late postoperative course).

Additional analgesia will be provided as required according to the following scheme:

• First line reserve: metamizole, maximum 4 g/24 h

• Second line reserve (if necessary): morphine, 1-2 mg, delivered intravenously

The use of additional analgesics will be documented.

### Trial interventions

Patients will be randomized according to the following scheme:

Primary arm 1: Patients with a unilateral inguinal hernia

secondary arm 1: mesh fixation with tissue glue

secondary arm 2: mesh fixation with staples

Primary arm 2: Patients with bilateral inguinal hernias

secondary arm 1: right side, tissue glue; left side, staples

secondary arm 2: right side, staples; left side, tissue glue

### Methods for reducing bias

The patients will be randomly assigned to the treatment, and the patients will be blinded to the assigned treatment. In primary arm 2 (patients with bilateral hernias), the bias of individual pain perception can be eliminated, because a single individual decides (blindly) which side is more painful.

The treatment assignment will be based on a block randomized list (one for each primary arm) with variable block sizes (between 2 and 6 patients per block). After each patient signed the informed consent, his name will be entered into the study database. At the beginning of surgery, the patients scheduled for unilateral repair will be examined laparoscopically to determine whether the other side also requires repair. The final decision for uni- or bilateral repair can only be made after this intra-operative examination. Thus, randomization will occur during surgery by contacting the study nurse to receive the treatment allocation. In the absence of the study nurse, the data manager can provide the allocation information. The data manager generates the randomization list and maintains a secured copy of the assignment list. The pain scores are obtained by nurses or physicians that are not aware of the treatment assignment (observer blinding).

In the case of unforeseen postoperative complications, the treating physician (surgeon) will know the treatment assignment and can be reached by phone. Furthermore, the data manager can unblind the assignment when necessary. Any unblinding will be recorded in the study documentation.

### Sample size calculation

The sample size was calculated under the hypothesis that either glue fixation or staple fixation is superior for the primary endpoint (= pain after 24 h)(two-sided analysis). Lovisetto reported a mean VAS pain score of 1.9 for glue fixation and 2.6 for staple fixation one month after TAPP repair
[19]. The observed difference of 0.7 is usually considered to be of no clinical relevance. We thus assumed a difference of 1 as a clinically relevant difference. Standard deviation was estimated to be equal 1, resulting in a standardized effect size of 1 which generally is considered clinically relevant. The sample size calculation was performed as two-sided analysis with a type I error of α = 0.05 and a power of (1-β) = 0.90.

Based on these assumptions, we calculated that 23 patients per arm would be required for unilateral hernias (t-test for two independent samples with common variance). Assuming a drop-out rate of 20%, the total number of patients needed per arm is 29, resulting in a total of 58 patients with unilateral hernias. For the second arm with bilateral hernias we calculated that 19 patients would be required (t-test for paired samples), assuming an intra-individual correlation of 0.2 (derived from a preliminary, unpublished analysis of patients with bilateral inguinal hernias that had undergone a Lichtenstein procedure). With a drop-out rate of 20%, a total of 24 patients with bilateral hernias would be required, resulting in a total of 82 patients for the entire study.

With an annual case load of approximately 100 in the previous years, we estimate that patient recruitment should be achieved within one or two years.

### Statistical analysis

The statistical analysis will be performed with SPSS Statistics for Windows (IBM Corp., Armornk, NY, USA). A two-sided p-value <0.05 will be considered statistically significant. Descriptive statistics will be used to analyze the baseline characteristics. For the superiority analysis of pain intensity at 24 h after surgery, the Mann−Whitney U and Wilcoxon tests will be applied, as appropriate. To adjust for multiple testing, the Hochberg procedure will be applied
[29].

Pain measurements performed at 4, 8, 12, 24, 36, 48 h after surgery by patients with unilateral and bilateral hernias will be analyzed in one mixed model to assess the mean ranks of the NRS scores with adjustments for time, treatment, and unilateral versus bilateral hernias. To compare other continuous secondary endpoints (e.g., operating time, length of hospital stay, postoperative administered analgesics, time to return to normal activity, and economic impact), the Mann−Whitney U and Wilcoxon tests will be applied, as appropriate. Chi-square statistics will be used to compare categorical secondary endpoints (e.g., incidence of chronic pain, rate of recurrence, and postoperative morbidity). Auxiliary, non-confirmatory analyses will be performed to assess the influences of baseline patient characteristics and treatment characteristics on the primary and secondary outcomes.

Intermittent missing values will be replaced by linear interpolation (e.g. post-operative pain values within 48 h after surgery). No interim analysis is planned for this study. Data from patients withdrawn from the study will be disregarded, unless exclusion is based on a postoperative patient request, and the patient agrees to the use of existing documented data.

The confirmatory analysis will be performed based on an intention-to-treat (ITT) design, and it will adhere to ITT principles. When a protocol violation occurs, a per protocol analysis (PP) will be performed for comparison.

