### Study objectives and endpoints

The primary objective of this trial is to show that after TAPP repair for unilateral and bilateral inguinal hernias the acute postoperative pain caused by mesh fixation with tissue glue is less than with staple fixation.

The primary efficacy endpoint of the TISTA trial is pain under physical stress at 24 h after surgery. Pain will be rated by the patient using a numeric rating scale (NRS). The NRS ranges from 0 to 10 in steps of one, with 0 representing no pain at all and 10 the worst imaginable pain. The NRS is comparable to the visual analogue scale (VAS) where the degree of pain is marked on a 10 cm long line. In practical terms, average NRS and VAS scores (in cm) can be considered equivalent. The patient is first asked to rate the pain at rest and then to rate it after physical stress. Physical stress is induced by a 90° bending of the hip joint on the operated side(s). The secondary endpoints of the trial and their definitions are summarized in Table 
1.

**Table 1 T1:** Secondary endpoints and definitions

**Secondary endpoints**	**Definitions**
Pain rated before surgery and at 4, 8, 12, 36, 48 h after surgery	Measured on a numeric rating scale from 0-10 at rest and upon bending the hip joint on the operated side
Operating time	Time, in minutes, from the first skin incision to the application of dressing
Length of hospital stay	Time, in days (with one decimal precision), from start of surgery to hospital release
Postoperative analgesic requirements	Amount (g/day) and type (paracetamol, metamizole, morphine) of analgesic required after surgery, before hospital discharge
Incidence of persistent pain (neuralgia)	Neuralgia defined as:
	• The presence of intermittent hyperesthesia, burning sensation, or jabbing pain in the ipsilateral, inguinal area nerves (genitofemoral nerve, lateral cutaneous femoral nerve, ilioinguinal and iliohypogastric nerve) [20,22,27]
	• Evaluation will be performed 14 days, 1, 3 and 12 months after surgery
	• The degree of pain will measured as described above
Postoperative morbidity	Categorized according to Dindo et al [28], and it includes:
	• Wound infection, defined as infections treated without further surgery and identified by clinical examination without microbiological confirmation
	• Hematoma or seroma formation, identified by clinical examination alone, before discharge from hospital, which does not require radiological confirmation

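### The 24 h pain analyses use ranks without the pre-operative score already collected, and name no difference in NRS points although the trial is sized on one point

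*Protocol article*

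**What the plan says.** The endpoint is defined under Study objectives and endpoints: "The primary efficacy endpoint of the TISTA trial is pain under physical stress at 24 h after surgery". It is scored on an integer scale from 0 to 10. Table 1 in the same section lists among the secondary endpoints "Pain rated before surgery and at 4, 8, 12, 36, 48 h after surgery", measured at rest and on bending the hip on the operated side. A baseline on the same measure as the primary endpoint is therefore collected.

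Under Statistical analysis, the confirmatory comparison is fixed in the sentence that opens "For the superiority analysis of pain intensity at 24 h after surgery": it names the Mann-Whitney U and Wilcoxon tests and no covariate. It is judged at two-sided 0.05 with a Hochberg adjustment. The scores from 4 to 48 h go into one mixed model for the "mean ranks of the NRS scores with adjustments for time, treatment, and unilateral versus bilateral hernias". Pre-operative pain is not among the listed adjustments. Baseline characteristics are described, and otherwise enter only auxiliary analyses labelled non-confirmatory.

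The Sample size calculation is written in points and uses t-tests: "We thus assumed a difference of 1 as a clinically relevant difference", with an SD of 1.

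**The concern.** Two things do not fit together.

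- **Unused baseline.** The pre-operative score is usually the first candidate for a covariate in a pain trial. Here it is recorded on the same scale and manoeuvre as the endpoint, yet it is left out of both the confirmatory test and the model. Randomization is blocked within hernia type only, so nothing else in the design deals with baseline pain. If it predicts 24 h pain, some precision is given up at no saving.
- **Different scales.** The trial is planned on a difference in points but analysed on ranks. A rank-test p-value, or a difference in mean ranks, does not tell a surgeon how many NRS points separate glue from staples, nor how that compares with the one point on which the trial was planned.

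**Working it through.** **Inputs from the Sample size calculation:** difference 1, SD 1, two-sided alpha 0.05, power 0.90, within-patient correlation 0.2 (bilateral), drop-out 20%.

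**Input not in the documents:** the correlation r between pre-operative and 24 h stress NRS. The 0.2 in the article is the correlation within a patient with bilateral hernias, which is a different quantity. I take r = 0, 0.2, 0.3 and 0.5.

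**1. The plan's own figures.**
- Unilateral, two-sample t-test with standardized difference 1: n = 22.02, rounded up to 23 per arm (power 91.2%). With drop-out, 23/0.8 = 28.75, so 29 per arm and 58 in total.
- Bilateral, paired t-test: SD of the difference = √(2 × (1 − 0.2)) = 1.265 and n = 18.84, rounded up to 19 (power 90.3%). With drop-out, 19/0.8 = 23.75, so 24.
- Total 58 + 24 = 82.

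All stated numbers reproduce, for t-tests on a mean difference.

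**2. What baseline adjustment could add (unilateral cohort).** The residual SD is SD × √(1 − r²), put into the same t-test formula. The power column ignores the one degree of freedom spent on the covariate.

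| r (assumed) | Variance removed, r² | Residual SD | Power at 23 per arm | n per arm for 90% power | 95% CI half-width (points) |
|---|---|---|---|---|---|
| 0 | 0% | 1.000 | 91.2% | 23 | 0.60 |
| 0.2 | 4% | 0.980 | 92.3% | 22 | 0.58 |
| 0.3 | 9% | 0.954 | 93.5% | 21 | 0.57 |
| 0.5 | 25% | 0.866 | 96.9% | 17 | 0.52 |

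The half-width is t(0.975; 43) × residual SD × √(2/23).

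**3. The planned rank test on an integer scale.** Simulation with 23 per arm, underlying means 2 and 3, SD 1, scores rounded to 0–10, 4,000 runs per row (simulation error about half a percentage point):

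| r (assumed) | t-test | Mann-Whitney | Baseline-adjusted linear model |
|---|---|---|---|
| 0 | 88.8% | 86.8% | 88.0% |
| 0.3 | 89.1% | 87.5% | 90.5% |
| 0.5 | 88.8% | 87.5% | 94.1% |

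The rank test costs 1 to 2 points of power against the t-test. Adjustment gains about 1 to 7 points over Mann-Whitney across this range.

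**4. An estimate in points.** In the unilateral cohort the interval would be about ±0.5 to ±0.6 points (step 2). In the bilateral cohort with 19 pairs the half-width is t(0.975; 18) × √(1.6/19) = 0.61. Both are narrow enough to be read against 1 point.

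**The case against.** The strongest defence is that nothing here is invalid. Unadjusted rank tests hold their error rate under randomization, chance baseline imbalance is already allowed for in that error rate, and ranks are a defensible choice for a bounded 11-step scale. This stands. So does the argument that the gain may be small: the eligibility criteria exclude chronic pain and most acute pain needing analgesics, which narrows the baseline spread, and standardized analgesia may loosen its link with 24 h pain.

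It is also fair that an article need not list every estimate, and that it nowhere says only p-values will be reported. The point survives because the article does more than stay silent: it names the rank scale for both the confirmatory test and the model.

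In the bilateral cohort, pairing already removes differences between patients, and the side is randomized. Moreover, "the patients scheduled for unilateral repair will be examined laparoscopically to determine whether the other side also requires repair", so a hernia found only then may have no pre-operative score on that side. A baseline adjustment could be impossible for exactly those patients.

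A reader might also infer that the trial is defective because it can reach significance below 0.7 points, given the remark "The observed difference of 0.7 is usually considered to be of no clinical relevance". On the plan's SD and t-tests, the smallest significant differences are 0.59 (23 per arm), 0.53 (29 per arm) and 0.61 (19 pairs). The documents do not support that inference:
- Any trial with 90% power at two-sided 0.05 becomes significant at about 1.96/(1.96 + 1.28) = 0.60 of its design difference.
- The thresholds belong to t-tests, not to the planned rank tests, and they ignore Hochberg. If that procedure covers the two cohorts and only one succeeds, 0.025 applies and they become 0.68, 0.61 and 0.71.
- The 0.7 is a VAS difference one month after surgery, not stress pain at 24 h.
- Baseline adjustment would lower the threshold further. Only a reported estimate answers the question of relevance.

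**Conclusion.** The point holds as a loss of precision and interpretability, not as an error. The sample size reproduces and the planned tests are valid.

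The part that needs no assumption is the mismatch of scales: the trial is sized on a difference in points, while the analyses named for early pain work on ranks. The part that rests on an assumption is the gain from baseline adjustment. It runs from nothing at r = 0 to 5.7 percentage points of power at r = 0.5 (96.9% − 91.2%), with the low end plausible in this population. It applies mainly to the unilateral cohort and the mixed model. The documents do not support a claim that omitting baseline biases the comparison, or that the bilateral analysis needs it.

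**What to change.** Amend the analysis wording before unblinding; the article reports recruitment as ongoing.

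- **Unilateral cohort:** compare 24 h stress NRS between fixations with a linear model adjusted for pre-operative stress NRS (ANCOVA). If ranks are to remain primary, use rank ANCOVA on that baseline.
- **Mixed model:** add pre-operative NRS as a covariate, and say how a side without a pre-operative score is handled.
- **Bilateral cohort:** keep the paired analysis. Adjust for the pre-operative difference between sides only as a sensitivity analysis, in patients with a score on both sides.
- **Both cohorts:** report the difference in NRS points with a 95% CI and read it against 1 point.
- **Sensitivity:** if a mean-based model becomes primary, keep the unadjusted Mann-Whitney and Wilcoxon tests as sensitivity analyses.

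The cost is wording. No new patients or measurements are needed, apart from the sides found at laparoscopy that may lack a baseline. The downside is a mean-based model on a bounded integer scale, which the rank analyses would check.

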	• Re-operation, defined as the need for re-operation during the initial hospital stay
	• Bleeding
	• Urinary retention, urinary tract infection
	• Pulmonary infection
	• Any serious deviation from the normal postoperative course
Time to return to normal activities	Time, in days, from hospital discharge to first working day
Relapse	Within 1 year of surgery
Economic impact	Calculated based on the following factors:
	• Cost for glue, staples, and instruments to apply glue or staples
	• If relevant: cost for excess operating time for the “slower” mesh fixation
	• Length of hospital stay (cost/day)
	• Medical leave of absence (converted into a monetary amount based on an average salary)

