## Discussion

This study was designed as a randomized trial with a two-by-two, parallel design. We aimed to compare patients with unilateral hernias that received mesh implants, fixed with either tissue glue or staples and to evaluate patients with bilateral hernias that received mesh implants fixed with tissue glue on one side and staples on the other side. In the latter group, the same patient will rate the pain associated with both methods; these ratings will not be influenced by inter-individual biases present in the unilateral hernia arm. To further reduce biases, both patients and observers (staff evaluating the pain) will be blinded to the assigned treatment.

We expect that mesh implants fixed with tissue glue will be associated with less postoperative pain, shorter hospital stay, and a shorter sick leave after the operation compared to implants fixed with staples. In addition to enhancing patient comfort, the tissue glue fixation will also have an economic impact, by reducing health care costs. Because we can evaluate both inter-individual and intra-individual biases in pain perception, this study will provide important insights for future studies that aim to investigate pain. This study will therefore provide novel information that is currently lacking in the literature.

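### The only analysis named for economic impact is a rank test, which does not estimate the mean cost difference that a statement about reduced costs needs (secondary endpoint, minor)

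*Protocol article*

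**What the plan says.** Table 1 (Study objectives and endpoints) lists economic impact as the last secondary endpoint. It is "Calculated based on the following factors": the cost of glue, staples and applicators; excess operating time for the slower fixation, if relevant; "Length of hospital stay (cost/day"); and "Medical leave of absence (converted into a monetary amount based on an average salary").

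The Statistical analysis section names one method for it, shared with the other continuous secondary endpoints, among them "postoperative administered analgesics, time to return to normal activity, and economic impact": the Mann-Whitney U and Wilcoxon tests, whichever is appropriate. No other analysis of costs is named.

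The Discussion, directly after a sentence on what the investigators expect, says that "the tissue glue fixation will also have an economic impact, by reducing health care costs".

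Trial interventions gives each unilateral patient one fixation method and each bilateral patient both, one per side.

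**The concern.** Whether a technique reduces costs is a question about total cost, which is the arithmetic mean per patient times the number of patients. Hospital stay and sick leave are bounded below and open above, so a few long stays or absences can carry much of the total. A rank test uses only the order of the costs. It discards how expensive the expensive cases are, and its p-value has no monetary unit.

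If costs are more spread out in one arm, the rank test can miss a real mean difference, can be significant when means are equal, or can favour the arm that costs more. Its p-value could then be reported as the answer to a question it does not address.

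Two features of the endpoint add to this. It mixes lost salary with health care costs, while the Discussion speaks of health care costs only. And a paired Wilcoxon test in bilateral patients, the natural reading of applying the two tests as appropriate, would need a cost per side. Stay and leave occur once per patient and cannot be assigned to one fixation.

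**Working it through.** **Inputs from the article.** Sample size calculation gives 23 evaluable patients per unilateral arm and 29 recruited. These are set by the pain endpoint: "We thus assumed a difference of 1 as a clinically relevant difference", with SD 1, in a "two-sided analysis with a type I error of α = 0.05 and a power of (1-β) = 0.90". They reproduce: a two-sample t-test has power 0.8997 at 22 per arm and 0.9125 at 23, and 23/(1 − 0.2) = 28.75, rounded up to 29. No mean, SD or target difference is given for costs, so **every cost distribution below is an assumption**.

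**Formulae.** For log-normal cost with log-mean μ and log-SD s, the median is exp(μ) and the mean is exp(μ + s²/2). For independent arms A and B, P(A cheaper than B) = Φ((μB − μA)/√(sA² + sB²)).

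**1. Equal medians, log-SD 1.0 against 0.6.** The ratio of means is exp((1.0² − 0.6²)/2) = exp(0.32) = 1.377, so one arm costs 38% more on average. In simulation with 29 per arm, Mann-Whitney rejects in about 5% of trials, which is chance level.

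**2. Medians 10 and 12, same log-SDs.**
- P(A cheaper) = Φ(ln 1.2/√1.36) = 0.562, so ranks favour A.
- Mean of A = 10 × exp(0.5) = 16.5; mean of B = 12 × exp(0.18) = 14.4. A costs more.
- Mann-Whitney is significant in favour of A in about 12% of trials with 29 per arm.

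**3. Equal means, unequal spread.** Mann-Whitney is significant in these shares of simulated trials:

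| Log-SDs | Per arm | Mann-Whitney | Welch t |
|---|---|---|---|
| 1.0 and 0.6 | 29 | about 29% | not tabulated |
| 0.5 and 0.3 | 23 | 9.8% | 5.6% |
| 0.8 and 0.3 | 23 | 32.2% | 8.8% |
| 1.0 and 0.3 | 23 | 50.7% | 11.4% |

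With 23 per arm and arm A 10% dearer on average, the test significantly favours A in 16.8% of trials (log-SD 0.8 against 0.3) or 35.4% (1.0 against 0.3).

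**4. Same shape in both arms (log-SD 0.5, 23 per arm).** The problem disappears. With equal means, Mann-Whitney rejects in 4.6%. With costs 20% lower in one arm, power is 29.8% for Mann-Whitney and 28.7% for Welch t; with costs 30% lower, 62.6% and 60.4%.

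**5. What a mean comparison achieves in scenario 1.** A percentile-bootstrap 95% interval excludes zero in about 22% of trials and covers the true difference in about 89% with 29 per arm; with 23 per arm, about 18% and 87%. A Welch t-test detects the 38% difference in about 11% with 29 per arm.

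**The case against.** A reader might infer that the trial cannot support any statement on reduced costs. The documents do not bear that out. Costs are built up from collected components, so the same data give arithmetic means and their difference whichever test supplies a p-value. The article does not say that means will go unreported.

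Other points against pressing the matter:

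- The article condenses a fuller document and names no effect estimate for any endpoint, including the primary one. The absence of an estimate and interval is therefore no fault in itself. **This stands.** What remains open to criticism is the test that was chosen.
- The cost sentence in the Discussion is an expectation about a secondary endpoint, with no hypothesis, power or decision rule attached. **This stands** and limits the severity.
- The harm appears only if spread differs between arms, and nothing in the article suggests that it will. **This stands as a limit on size.** Equally, nothing justifies assuming equal shape, and even then the rank test gives no amount of money.
- A mean comparison would also miss most differences at this sample size, and its interval under-covers with skewed costs. **This stands.** The remedy makes the analysis answer the right question; it does not add the information needed to prove a saving.

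**Conclusion.** The point holds in a limited form. The one analysis the article names for economic impact is poorly matched to the question the article attaches to that endpoint. It follows from the definitions that a rank test does not compare mean costs. How much this would matter rests on assumed log-normal costs with unequal spread: under those assumptions the test can overlook a 38% mean difference or favour the dearer arm, and with equal shapes it agrees with a mean comparison in direction and power. That within-patient total cost cannot be split between fixations in bilateral patients needs no distributional assumption.

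Severity is minor. The primary endpoint, the sample size and the confirmatory pain analysis are untouched.

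**What to change.** In the Statistical analysis section, take economic impact out of the list of rank-tested endpoints and state:

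- The main cost analysis is the difference in arithmetic mean cost per patient, glue minus staples, in the unilateral cohort, with a 95% confidence interval (for example a bias-corrected bootstrap).
- Each cost component is shown separately by arm, with sick leave reported apart from health care costs.
- A rank test, if kept, is descriptive only.
- No within-patient test of total cost is made in bilateral patients.

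This costs a few sentences and a bootstrap on data already planned for collection. The downside is a wide interval that may fall short of nominal coverage with 23 to 29 per arm and skewed costs. The report should say so, and should not read an interval that includes zero as evidence of equal costs.

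### Categorical secondary endpoints have no paired test for the bilateral cohort, and per-patient secondary endpoints have no glue-staple contrast there at all

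*Protocol article*

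**What the plan says.** Under Trial interventions, one bilateral sub-arm is "right side, tissue glue; left side, staples" and the other is the mirror image. Only the side is randomised, and every bilateral patient receives both fixations.

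Under Statistical analysis there are two rules for secondary endpoints other than early pain:

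- Categorical: "Chi-square statistics will be used to compare categorical secondary endpoints (e.g., incidence of chronic pain, rate of recurrence, and postoperative morbidity". No paired version is named and no cohort is specified.
- Continuous: "other continuous secondary endpoints (e.g., operating time, length of hospital stay, postoperative administered analgesics, time to return to normal activity, and economic impact" are compared with Mann-Whitney U and Wilcoxon tests, whichever suits. Again no cohort is specified.

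Table 1 fixes the unit of observation. Neuralgia is defined on the nerves of the groin on the same side. Operating time runs from first incision to dressing, stay from surgery to release, and return to activity from discharge to first working day. Analgesic use is an amount per day. Cost includes stay and medical leave. Morbidity includes items with no side, such as "Urinary retention, urinary tract infection" and pulmonary infection.

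The Discussion expects shorter stay, shorter sick leave and lower cost with glue, without saying which patients can show this.

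**The concern.** The bilateral cohort exists so that each patient is his own control. Two kinds of secondary endpoint do not fit the tests named for them.

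1. **Binary outcomes per groin.** The glue groins and staple groins in this cohort belong to the same men. An ordinary chi-square has no place for that link, so it uses the wrong variance for the difference. The continuous endpoints are given a paired alternative; the binary ones are not.
2. **Outcomes with one value per patient.** A bilateral patient has one length of stay and two treatments. A signed-rank test has no pair to work on. A Mann-Whitney or chi-square test between the two bilateral sub-arms compares glue on the right with glue on the left, which says nothing about glue against staples.

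At stake are the precision of the recurrence and chronic-pain comparisons, and the basis of any claim on stay, sick leave, cost or systemic complications.

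**Working it through.** **Plan's own figures.** Inputs from Sample size calculation: "The sample size calculation was performed as two-sided analysis with a type I error of α = 0.05 and a power of (1-β) = 0.90". The target is a one-point gap on the pain scale, taken with this spread: "Standard deviation was estimated to be equal 1, resulting in a standardized effect size of 1".

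- Unilateral, two-sample t-test: 22.02, so 23 per arm (power 91.2%); 23/0.8 = 28.75, so 29 per arm and 58 in all.
- Bilateral, paired t-test with the plan's correlation of 0.2: SD of the difference = √(2 × (1 − 0.2)) = 1.265. This needs 18.84, so 19 patients (power 90.3%); 19/0.8 = 23.75, so 24.
- Total 58 + 24 = 82. All reproduce. The paired calculation shows that the plan recognises the pairing for the primary endpoint.

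**Binary outcomes per groin: direction and size of the error.** For n pairs with event probability p on each side and within-patient correlation ρ, the true variance of the difference in proportions is 2p(1 − p)(1 − ρ)/n. The chi-square assumes 2p(1 − p)/n.

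- SE overstated by 1/√(1 − ρ): at ρ = 0.2, 1/√0.8 = 1.12.
- Large-sample size of a nominal 5% test is 2 × [1 − Φ(1.96/√(1 − ρ))]: 2.8% at ρ = 0.2 and 0.56% at ρ = 0.5.

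For 24 pairs, the joint probability of events in both groins is p₁p₀ + ρ√(p₁(1 − p₁)p₀(1 − p₀)). Summing the multinomial over all tables gives the following. The chi-square statistic is (x₁ − x₀)²/[2n p̄(1 − p̄)]. McNemar is (b − c)²/(b + c) on the discordant pairs.

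| Assumed event rate | ρ | Chi-square size | Asymptotic McNemar size |
|---|---|---|---|
| 10% | 0.2 | 2.6% | 3.8% |
| 20% | 0.2 | 3.2% | 4.8% |
| 30% | 0.2 | 3.0% | 4.4% |
| 10% | 0.5 | 0.6% | 1.6% |
| 20% | 0.5 | 0.8% | 4.2% |
| 30% | 0.5 | 0.7% | 4.9% |

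If the 24 pairs are pooled with 29 unilateral patients per arm, the chi-square size is 4.0-4.2% at ρ = 0.2 and 2.7-2.8% at ρ = 0.5.

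Power for 10% against 30%, 24 pairs:

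| ρ | Chi-square | Asymptotic McNemar | Exact McNemar |
|---|---|---|---|
| 0.2 | 42% | 47% | 29% |
| 0.5 | 39% | 72% | 34% |

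The second row is close to the extreme. With these rates the largest possible correlation is (0.10 − 0.03)/√(0.09 × 0.21) = 0.51, so nearly all discordant pairs point one way. At ρ = 0 the order reverses (43% for chi-square, 38% for McNemar). The gain depends on positive correlation.

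**Outcomes with one value per patient.** In the bilateral cohort each man received one glue and one staple fixation, so treatment does not vary between men. Of the 24, none adds a glue-staple contrast. The comparison rests on 29 against 29, or 23 against 23 after the planned drop-out. The price of the fixation materials is the one part of cost that can be assigned to a side.

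**The case against.** **The plan does recognise pairing.** This is correct for pain. The bilateral cohort is sized with a paired test, pain at 24 h may be tested with a paired rank test, and the 4-48 h scores go into a mixed model. A reader might infer that all the secondary tests ignore the design; the text does not support that. The groin-level point is confined to categorical endpoints.

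**McNemar is itself loosely a chi-square statistic, and an article may leave such detail to the full protocol.** The wording does not exclude it. But the same section names a paired and an unpaired test for continuous endpoints and one method for categorical ones, so the stated rule as it reads is the ordinary test.

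**The error is on the safe side.** This stands. One might read the point as inflated false positives for relapse or chronic pain; the calculation shows the opposite.

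**Exact tests make the conservatism worse.** This also stands. At correlation 0.2 and event rates of 10-30%, exact McNemar has size 0.3-1.9%, against 2.6-3.2% for chi-square, and less power (29% against 42%). Small expected counts are therefore not a sound reason to prescribe exact tests here. In unilateral patients (29 against 29) the chi-square is close to nominal at assumed rates of 10% and 20% (5.4% and 4.8%). It falls to 2.7% at 5% and 0.3% at 2%, where Fisher's test is lower still (0.1% and about 0%).

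**The freedom to choose the suitable test could mean Mann-Whitney in unilateral patients only.** It could, for continuous endpoints. The section does not say so, and neither named test works in the other cohort. A reader might go further and suppose that bilateral patients will be counted under both treatments, shrinking an effect to 29/(29 + 24) = 55%. The plan states no such analysis.

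**Conclusion.** The point holds in two limited parts.

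- **Groin-level binary outcomes:** the test named does not fit paired groins. The consequence is conservatism and lost power. The loss is small at correlation 0.2 (42% against 47% in the example) and large only if the correlation is high. Event rates and binary correlations are assumptions. The plan's 0.2 comes from an unpublished analysis of patients after a different repair and is used for pain scores, not for relapse or neuralgia. Treating relapse and haematoma or seroma as side-specific is a reading of their nature; Table 1 says so only for neuralgia.
- **Per-patient outcomes:** this is the firmer part and needs no assumption about rates. No test in the plan gives a glue-staple comparison in the 24 bilateral patients. The expected benefits in stay, sick leave and the corresponding costs can rest only on the 58 unilateral patients. The Discussion voices an expectation, not a confirmatory claim on 82, so this is a missing limit rather than a false result.

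Only secondary endpoints are touched. The primary test, the mixed model and the sample size stand.

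**What to change.** Change the wording of Statistical analysis before the data are unblinded:

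1. **Groin-level binary endpoints** (neuralgia, relapse, haematoma or seroma): asymptotic McNemar in bilateral patients and chi-square in unilateral patients, or one model for both cohorts clustered on patient, with risk differences and confidence intervals. If exact McNemar or Fisher is preferred for sparse tables, state the added conservatism and loss of power. The clustered model has not been checked here for rare events in 24 pairs.
2. **Per-patient endpoints** (operating time, stay, analgesics, return to work, the stay and leave parts of cost, systemic complications): test glue against staples in the unilateral cohort only, and report the bilateral cohort descriptively.
3. List which morbidity items are recorded per groin and which per patient.

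The cost is text only, with no new data and no change in numbers. The downside is that per-patient claims are openly based on 58 patients rather than 82, and on 46 after the planned drop-out. McNemar also gives up a little power if the two groins turn out to be uncorrelated.
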